### Intervention

The LHS intervention has been based on concepts from the model of delivery used by the CEG. The LHS intervention in this context will consist of 3 elements:

**Data management software—the Active Patient Link tool:** to enhance data-driven quality management, the research team has developed the APL tool (figure 4)—an online platform that uses national routine EHR data to visualise actionable quality indicators for frontline healthcare workers. In addition to providing dashboards for performance monitoring, the APL tool includes a recall page that enables clinicians to identify and prioritise patients in their catchment population based on clinical risk. We will iteratively adapt the tool throughout the trial as the staff learn how to use it and will expand its use to more conditions. As many NCD patients present first with HTN, we started with HTN, but we recognise that this frequently co-occurs in people with diabetes, which is why we will focus on diabetes subsequently. Patients with diabetes and HTN are at risk of CKD, and therefore, we will then expand to CKD. As years go on, and if this approach is successful, we anticipate that staff will request add-ons for respiratory, liver and heart disease.At a local level, the use of the tool will vary according to clinical need. PCUs will be able to generate patient lists based on specific clinical criteria to support structured recall; they will be able to view a detailed page of information about the patient’s current medications, laboratory results and clinical observations; and they will be able to identify which patients have been lost to follow-up. The tool therefore supports proactive, individualised care planning and targeted outreach.The feasibility, acceptability and appropriateness of the APL tool and facilitation will be measured through the semi-structured interviews and a short survey. The survey has been devised to capture aspects of tool usability that are not covered by the interviews.**Facilitation support:** to foster sustainable change and embed QI into everyday practice, structured facilitation support through both online and in-person engagements is being provided for the 16 intervention PCUs. Trained facilitators—a doctor, nurse and psychologist—will engage frontline workers in regular meetings to build capacity, offer tailored guidance and co-reflect on local data insights generated by the APL tool. These meetings will occur every 2 weeks, or within a time frame that suits the needs of the PCU. These facilitation sessions will serve multiple purposes: helping frontline staff interpret quality indicators, identify areas for improvement, plan and implement change ideas, and navigate operational challenges. This will ensure that frontline teams remain supported, engaged and empowered throughout the quality improvement cycle, reinforcing a culture of learning and accountability within primary care settings. The facilitation will remain in place for participating PCUs throughout the entirety of the study period.**Education around embedding a culture of quality improvement into clinical practice:** the research team will conduct stakeholder consultation workshops with frontline healthcare workers from 16 sites over the 4-year trial period. The ‘stakeholders’ in question are nurse practitioners, public health officers, primary care physicians and governmental stakeholders such as the Ministry of Public Health and the local provincial public health office. These workshops happen once yearly, introducing the concept of a LHS, providing the research team with an understanding of routine clinical workflows, identifying gaps in the management of NCD cases and helping frontline staff collaboratively design actionable quality indicators. After a year of implementing LHS strategies, the 16 intervention sites will serve as community champions—sharing their lessons learnt, successful strategies and practical experiences with other practices across their province.Additionally, findings from the workshops will be reinforced during the facilitation support visits by the research team to ensure contextual understanding, build trust with local staff, validate findings from the workshops and support the co-design of tailored quality improvement strategies aligned with each site’s needs and capabilities.

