Complete/on-time: patients who attend appointments every 6 months for their CKD stages 1–4 review within a 12-month period.Delayed: patients who have routine review appointments for their CKD stages 1–4 booked later than scheduled within a 12-month period.Lost: patients who are lost to follow-up without an appointment scheduled for routine CKD stages 1–4 review within a 12-month period.

The QI activity metrics that will be used within the realist evaluation include:

Number and frequency of clinical team meetings in each intervention site.Frequency of scheduled review of national KPIsNumber and professional roles of participants in these meetings.Number of individuals trained in using the APL tool in the context of QI and their professional roles.Quantitative feedback from training sessions—using a tool developed to collect feedback both for the tool development and facilitation training sessions.Total number of datasets used for QI projects.Volume of missing data within these datasets.

Data collection methods for these metrics will be driven by local practice around documentation of team activity—usually this is in the form of 6 monthly meetings with the provincial public health office. Baseline data for chosen metrics will be compared with data collected after a minimum of 3 months. This data will support the development of potential mechanisms as part of the programme theory; helping to triangulate service planning and quality improvement activities with staff perceptions of the LHS intervention.

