### Data analysis

Quantitative data will help identify where outcomes occur, while qualitative data will explain how and why these outcomes are achieved, providing a richer understanding of the relationships between contexts, mechanisms, and outcomes. This mixed methods approach will involve:

Comparing data types—quantitative patterns will be triangulated with qualitative insights to identify consistencies, contradictions and explanatory mechanisms.Iterative refinement of context-mechanism-outcome (CMO)—quantitative data will help identify where outcomes occur, while qualitative data will explain how and why these outcomes are achieved, providing a richer understanding of the relationships between contexts, mechanisms, and outcomes.

Where possible we will analyse mixed methods data concurrently to allow thematic sampling of themes within the interviews. Using the CMOs we will develop a final programme theory.

Interview data and documents will be coded using a realist logic of analysis. A reflexive diary will be kept during the qualitative analysis. Methodological rigour and validity will be maintained by having 10% of transcripts independently coded by another researcher. The qualitative data will be examined for CMO configurations, with a particular focus on the (C) and (M): does improved access to data and facilitation support within a collaborative environment (C) provide staff with the tools to adopt data-driven interventions and embed quality improvement culture in their daily clinical care (M)?

Our quantitative data analysis will include outcomes relating to improvements in population NCD burden and consistent use of improvement methodology in clinical care. An initial exploratory review of whether QI activities form a part of the PCU workload will be carried out. We will then perform a baseline analysis both for PCU demographics and their baseline QI activity, to be able to measure change in the outcomes.

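### The QI activity counts come from local documentation, and facilitation falls between the two readings, so a change in recording could be read as a change in activity

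*Protocol article*

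**What the plan says.** The section Quality improvement outcome and activity metrics lists measures that include "Number and frequency of clinical team meetings in each intervention site", how often national KPIs are reviewed, who attends and in what role, and how many datasets feed QI projects. On their source it says "Data collection methods for these metrics will be driven by local practice around documentation of team activity", and adds that "usually this is in the form of 6 monthly meetings with the provincial public health office". On the comparison it says "Baseline data for chosen metrics will be compared with data collected after a minimum of 3 months". The Data analysis section takes a reading of "baseline QI activity, to be able to measure change in the outcomes".

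The Intervention section states that "structured facilitation support through both online and in-person engagements is being provided for the 16 intervention PCUs". On timing it says "These meetings will occur every 2 weeks, or within a time frame that suits the needs of the PCU", and one aim it gives is "reinforcing a culture of learning and accountability within primary care settings".

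The article gives no common definition of a countable meeting or review. It does not say whether facilitation sessions count as team meetings, and it describes no check on how complete the records are at either reading.

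**The concern.** A before-after count measures change in activity only if the way of counting stays the same. Here the counting instrument is the site's own record-keeping, and the intervention between the two readings acts on the same teams that keep those records. A small unit that used to meet informally and now minutes its meetings would show a rise without doing more QI. If facilitation sessions are entered as team meetings, delivery of the intervention would be counted as a response to it.

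Consistent use of improvement methods is one of the outcomes in the initial programme theory and in the quantitative analysis. The activity metrics are meant to support candidate mechanisms and to be set against staff perceptions. If part of the change is only recording, the counts could appear to confirm a mechanism that did not operate. The refined programme theory is the evaluation's main product.

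**Working it through.** The article gives no sample size, error rate or expected change for these metrics, so there is no figure of its own to reproduce. The check has three parts.

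**1. Is the instrument constant?** Three statements are set side by side: the source follows local documentation practice; baseline is compared with a later reading to measure change; facilitation runs between the readings. Nothing in the article holds recording fixed across them. Other data sources only partly help:
- The HDC log-in record (Participant surveys) does not depend on site paperwork, but it measures tool uptake, not meetings or reviews.
- The training-feedback instrument covers one metric.
- Interviews, district minutes and the exploratory review of whether QI is part of PCU workload may reveal undocumented work, but no step uses them to adjust or qualify the counts.

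**2. Do the windows match the source?** Using the article's own intervals:
- 6-monthly meetings expected in a 3-month window: 3 / 6 = 0.5.
- Facilitation meetings in 3 months (13 weeks) at the nominal 2-weekly schedule: 13 / 2 = 6.5.
- Facilitation meetings in 6 months (26 weeks): 26 / 2 = 13, against one 6-monthly meeting.

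A follow-up at the 3-month minimum may therefore contain no provincial meeting at all. Whether facilitation sessions are included could also dominate a meeting count.

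**3. How large could a pure recording effect be?** Let r0 and r1 be the shares of real activity that are recorded before and after. Then

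apparent ratio = true ratio × (r1 / r0).

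The shares below are assumptions; the article gives none. With true activity unchanged (true ratio = 1):

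| r0 → r1 | Apparent ratio |
|---|---|
| 60% → 70% | 0.70 / 0.60 = 1.17 |
| 60% → 80% | 0.80 / 0.60 = 1.33 |
| 50% → 80% | 0.80 / 0.50 = 1.60 |

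Read the other way, an observed 1.5-fold rise implies a true ratio of 1.5 × r0 / r1: 1.5 with unchanged recording, 1.12 at 60% → 80%, 1.0 at 60% → 90%, and 0.94 at 50% → 80%.

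To judge whether such shifts would stand out from chance, 20,000 simulated data sets used 16 sites and Poisson counts with constant true activity. With B and A the recorded totals before and after, z = (A − B) / √(A + B). At an assumed 6 true events per site per period, the share of runs with z > 1.96 was:
- about 2% with recording unchanged at 60%
- 13% at 60% → 70%
- 38% at 60% → 80%
- 73% at 50% → 80%

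For 60% → 80%, the share runs from 22% at 3 events per site to 65% at 12. The article plans no such test; this is only a gauge of how easily a recording shift could look like a real increase.

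**The case against.** The strongest reply is that the source is less haphazard than the quoted clause suggests. The same sentence names the usual form, a recurring meeting with an outside authority. A reader might infer that each site is measured by whatever it happens to write down; the article does not support that. The word usually still leaves room for variation, and nothing ties the comparison to that one source in both periods.

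Second, a reader might infer that sites will be ranked on these counts, so that poor baseline recorders are mistaken for the strongest adopters. The sentence about sites with most and least activity stands before the QI metrics list and most directly concerns the patient follow-up classifications. The use stated for the activity metrics is to support mechanisms and triangulation. A ranking on these counts is not established.

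Third, nothing in the article says that facilitation will increase record-keeping. Facilitation may be online or in person, at a pace that suits the unit, and its listed purposes are interpreting indicators and planning change. The upward direction is therefore an inference. It is a reasonable one, given the stated aim of a culture of accountability.

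Fourth, the metrics are descriptive and are read alongside interviews, and the limitations section concedes observation bias and recording errors. That lowers the stakes. The concession is general, however, and does not address recording that changes with the intervention.

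Finally, a published article may leave collection forms to a fuller protocol. A missing form would not be a finding. Here, though, the text positively chooses local documentation as the source and fixes the comparison made from it.

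**Conclusion.** The point holds as a moderate weakness. As written, the comparison cannot separate a change in QI activity from a change in what is recorded, or from facilitation meetings entering the count. The bias is plausibly upward, but its size cannot be derived from the article. The fold-changes above show what assumed shares would produce and are not estimates for these sites. A reader should not conclude that a several-fold artefact is expected.

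The exposed items are team meetings, KPI reviews, attendance and roles, and datasets used. Numbers trained on the tool reflect delivery of the intervention, and training feedback has its own instrument, so both are little exposed. The trial's clinical outcomes come from the EHR and are not touched by this point.

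**What to change.** - Give one definition of each counted item and apply it at all 16 sites.
- Restrict before-after comparisons to items captured from the same source in both periods, for example the 6-monthly provincial meeting record.
- Use equal windows at baseline and follow-up, each covering at least one 6-monthly cycle.
- Count facilitation meetings separately from the unit's own team meetings.
- Describe any other before-after difference as a change in documented QI activity.

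A common prospective log could be added for the follow-up readings. A look-back form for baseline should be supporting information only: the trial began in July 2025, so staff already exposed to the intervention would be recalling the earlier period.

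The cost is a little staff time and fewer items that can be compared before and after. A 3-month reading could still be reported descriptively, but it would not serve as the comparison for items recorded every 6 months.

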### Data analysis

Quantitative data will help identify where outcomes occur, while qualitative data will explain how and why these outcomes are achieved, providing a richer understanding of the relationships between contexts, mechanisms, and outcomes. This mixed methods approach will involve:

Comparing data types—quantitative patterns will be triangulated with qualitative insights to identify consistencies, contradictions and explanatory mechanisms.Iterative refinement of context-mechanism-outcome (CMO)—quantitative data will help identify where outcomes occur, while qualitative data will explain how and why these outcomes are achieved, providing a richer understanding of the relationships between contexts, mechanisms, and outcomes.

Where possible we will analyse mixed methods data concurrently to allow thematic sampling of themes within the interviews. Using the CMOs we will develop a final programme theory.

Interview data and documents will be coded using a realist logic of analysis. A reflexive diary will be kept during the qualitative analysis. Methodological rigour and validity will be maintained by having 10% of transcripts independently coded by another researcher. The qualitative data will be examined for CMO configurations, with a particular focus on the (C) and (M): does improved access to data and facilitation support within a collaborative environment (C) provide staff with the tools to adopt data-driven interventions and embed quality improvement culture in their daily clinical care (M)?

Our quantitative data analysis will include outcomes relating to improvements in population NCD burden and consistent use of improvement methodology in clinical care. An initial exploratory review of whether QI activities form a part of the PCU workload will be carried out. We will then perform a baseline analysis both for PCU demographics and their baseline QI activity, to be able to measure change in the outcomes.

### Patient and public involvement

The realist evaluation workstream will involve patient and public involvement (PPI) for both patients and staff. We will conduct PPI workshops throughout the implementation and evaluation process to test the feasibility and acceptability of the LHS for both populations. Our methods and dissemination will be guided by UK National Institute for Health Research and Guidelines International Network reporting standards for PPI.^33 34^

We have also had substantial input from our other stakeholders during the development of the intervention: the Thai Ministry of Public Health (at national, provincial and district levels), the Thai WHO and the Thai Primary Care Support Office. This group of stakeholders has provided input into both the scientific and practical aspects of implementing the LHS intervention.

Sourcing from each of the intervention units, the CMU and Queen Mary University of London (QMUL) teams will train a network of clinical and community champions who will support the intervention primary care units to deliver the LHS and engage with patients and the public. Champions will be given clear role descriptions of what patient engagement is in the context of quality improvement. We will co-produce locally relevant educational materials and guidelines for healthcare providers and patients.

### Strengths, limitations and future directions

Using a mixed-methods approach for this realist evaluation to complement the findings from the trial will give a rich understanding of the mechanistic and contextual factors contributing to trial outcomes. This evaluation will provide specific as well as generic learning about the adoption of data-enabled innovative tools and their use in practice for health improvement in an LMIC setting. The focus on both robust quantitative and qualitative methodology will give insight into how human and organisational factors contribute to changes in NCD management and can be sustained in practice. Other strengths of our study include previous CMU collaboration with the Thai Ministry of Public Health, LSHTM and the WHO to lead work integrating electronic patient records into care pathways for NCDs.^3 35^ CMU has access to pseudonymised patient level EHRs for all individuals residing in Lampang and Chiang Mai provinces—two of the largest provinces in northern Thailand and cover a wide range of rural and urban contexts, therefore improving generalisability of results.

Limitations include the possibility of a reporting bias or observation bias where mechanisms are partially shaped by the presence of the research team. The quantitative analysis relies on routinely collected data which may include recording errors and missing data. The qualitative analysis will identify underlying mechanisms, but is unlikely to be fully understood due to cultural factors around communication, hierarchy and external evaluation, particularly in the context of a UK-Thai research collaboration. This may limit the extent to which problems or concerns are reported by staff.

### Comparison with existing literature

The LHS approach has been internationally recognised as a vital part of driving better health outcomes; however, there is a continuous need to build up the evidence base about how to help LMICs use this approach in an effective way.^28^ Our study has been set up to develop and pilot a LHS intervention that already has an evidence base of success in the UK.^36^ It is novel in its approaches of using existing methods and contextualising them in an LMIC setting with differing cultural norms and working patterns.

The LHS approach acts on learning from previous community interventions aimed at improving NCD management. The CMU team have recently implemented pilot programmes in Lampang province to improve the management of HTN and diabetes in primary care.^37 38^ Interventions included (1) co-design of simple education programmes and treatment protocols, (2) training of 53 primary care teams comprising >600 people, (3) monitoring of outcomes and (4) process evaluation using EHRs. The programme improved control of HTN and diabetes, improved access to treatment and care by empowering nurses and pharmacists to prescribe treatment, reduced variation between practices and reduced treatment inertia.^35^ Furthermore, the treatment protocols developed for the interventions were endorsed by the Thai Ministry of Public Health.^38^

Despite the success of the pilot programmes on several fronts, the new approaches were not continued, largely due to lack of knowledge around how to translate the approach for use in routine clinical practice over the longer term. This paper describes the design of a mixed-methods realist evaluation that aims to understand the contextual factors leading to successful implementation of a LHS intervention.
